### Inclusion and exclusion criteria

Eligible adolescents from the assigned schools will be asked to take part in the study. There are only two criteria for inclusion in the study: Participants must be aged between 11 and 14 years and in the 6th or 7th grade. We chose this age group because epidemiological data show that the end of childhood and the beginning of adolescence represents the period with the highest risk of onset of NSSI [22]. Accordingly, the first rise in incidence rates can be determined around the age of 14 years. Based on the rationale of universal prevention, a program should start before this period, keeping in mind that a universal prevention approach should start before a disorder develops [23]. Likewise, only two exclusion criteria will be applied: lack of informed consent from the adolescents or their relatives, and currently receiving individual psychotherapy because of a mental disorder. If participants report being in individual psychotherapy, to avoid stigmatization, they will still attend the training together with their classmates, and their data will be collected but saved separately. Thus, these participants will still be able to see information about their results, but these results will not be included in the data analysis. This procedure was chosen due to potential confounding effects between individual psychotherapy and the prevention program.

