After the feasibility stage, the main study will start. First of all, the schools for the main study will be chosen by the Ministry of Education and Cultural Affairs. The respective school principals will then be contacted to ensure that the implementation of the study will run smoothly. This will be followed by a personal meeting with the teaching staff and the study team to inform about the rationale, aims, and study procedure. At this point, schools will not yet have been randomly assigned to a trial group. This should prevent any bias due to motivational effects during the recruitment. Once schools have given consent, pupils and parents will receive information about the study in the following order: (1) An information evening (1 ½ h) about the study will be held for parents and pupils. (2) Subsequently, parents and participants will once again receive all information in writing and the consent form via mail or e-mail. (3) To give the participants another opportunity to ask questions, information about the study will be provided again (during a regular lesson) before data collection, and the presence of the consent forms will be checked. The written and oral information will include the following: background and objectives of the study, information about the prevention program (DUDE) and minimal intervention, benefits and possible risks of participation, data collection procedures, and data security procedures. After parents and adolescents have received the required information, informed consent will be obtained. The parents and participants will confirm with their signature that they have read and understood the provided information and that they are willing to participate. Nevertheless, they will be able to withdraw from the study at any time without any consequences for subsequent school matters or medical care (see also the “Ethical issues and dissemination” section). Next, schools will be randomized. Before the baseline measurement, pupils will be checked for eligibility and the booklets (“Stress-free through the school day”) will be handed out. Seven days (± 3 days) after the baseline measurement, DUDE will conducted in treatment groups 1 and 2 and will be integrated into the normal school schedule.

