Given the very large number of over 3000 participants, the measurements and execution of DUDE will be split into two time points. We aim to begin in November 2021, and the second round of assessment should take place around March 2022. However, due to the SARS-Covid-19 pandemic, delays are possible. To ensure that enough individual pupils give their consent to participate, the DUDE training will be integrated into the regular school day, during lesson time, to make participation more attractive to the students.

As mentioned above, to prevent bias, 16 schools will be randomly (cluster randomization, see the “Discussion” section) assigned to DUDE or to the active control group, with eight schools per group, using cluster randomization. Within the treatment group, there will be a secondary randomization into treatment groups 1 or 2. Enrolment, generation of allocation sequence, and assignment of schools will be carried out using the software SAS by an independent member of the institute not involved in the project. The schools will be informed about their group affiliation via e-mail and telephone call immediately after randomization. Nevertheless, blinding is not completely possible, as schools cannot be blinded to the different nature of the interventions. Blinding of the researchers is also not possible because the treatment group will receive DUDE in addition to the minimal intervention.

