### Data assessment

Data will be collected and assessed in cooperation with the Institute of Clinical Epidemiology and Biometry, University of Wuerzburg, Germany. The baseline assessment (T0) will take place after randomization and 7 days (± 3 days) before the subsequent start of the treatments. At the end of DUDE or 5 weeks after receiving the minimal intervention (± 7 days), the second measurement (T1) will be conducted. Further assessments will ensue 6 months (± 7 days; T2) and 12 months (± 7 days; T3) after the end of DUDE. After every measurement, the data will be screened for potential suicidality (see the “Emergency procedure” section). At T2, only a selection of the assessment measures will be used (see Fig. 2). We chose this procedure in order to check for iatrogenic effects which could occur immediately after the prevention [24], whereas protective effects, or rather efficacy, in universal prevention is expected later [25]. Additionally, we will evaluate how appealing DUDE is to the adolescents, as this might have an impact on the effectiveness of the program.

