### Emergency procedure

If the participants report serious suicidal thoughts in one of the measurements (assessed with the PSS, especially item 4 “Have you ever reached the point where you seriously considered taking your life or perhaps made plans how you would go about doing it?,” answering “Yes, within the last two weeks”), there will be an immediate (within 24 h) report back to their family. The family will be informed about the situation by one of the principal investigators and an appointment with a personal contact will be made at the Department of Child and Adolescent Psychiatry, University Hospital of Wuerzburg, or in one of the admission clinics with which the study team is cooperating. During this appointment, suicidality will be examined and, if necessary, a treatment offer will be made. If adolescents indicate serious suicidal thoughts within a unit of DUDE, psychologists or teachers will telephone the psychiatrist on duty to clarify the situation in a first step, and subsequently inform one of the principal investigators, as needed. Over the entire duration of the study, participants and their caregivers will be able to contact the Department of Child and Adolescent Psychiatry, University Hospital of Wuerzburg, in the case of mental health problems. This will also be indicated in the information letter.

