### Statistical analysis

The primary hypothesis will be addressed by using a univariate generalized linear mixed-effects model with logit link function for the probability of newly detected NSSI (measured dichotomously) at T3. To model the correlation within schools, schools will be included as random effects.

As secondary analyses, the generalized linear mixed model for the primary outcome will be adjusted for potential sociodemographic confounders (sex, socioeconomic status, mental stress due to the COVID-19 pandemic). In addition, we will adjust the baseline measure NSSI, although our analysis will only consider the incidence rate (newly detected NSSI in the last 12 months). Furthermore, based on the distribution of the secondary outcomes, differences in secondary outcomes between the two groups (treatment and intervention) will be compared. We will analyze emotion regulation (DERS-SF), suicidality (PSS), quality of life (KIDSCREEN-27), self-efficacy (RESE-R), general mental health (SDQ), depression (PHQ-9), and eating disorder pathology (SEED) using univariate mixed-effects models, and with non-parametric tests if necessary due to the data material.

Missing data and individuals who withdraw from the trial will be handled using an intention-to-treat (ITT) approach. All participants randomized will be considered in the analysis. In the case of dropout or missing data, we will use the multiple imputation method.

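### Psychotherapy status, which removes pupils from the analysis, and baseline NSSI are recorded after schools know their arm, and that removal conflicts with the rule to analyse everyone randomised

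*Protocol article*

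**What the plan says.** Two rules describe who is analysed. The Statistical analysis section states: "All participants randomized will be considered in the analysis". It adds: "In the case of dropout or missing data, we will use the multiple imputation method". The Inclusion and exclusion criteria make it an exclusion criterion to be "currently receiving individual psychotherapy because of a mental disorder". Pupils who report this still attend with their class and still give data, but "these results will not be included in the data analysis".

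The order of steps is set out in Procedure and randomization and in Data assessment. Consent comes first, then randomisation of schools. Then: "The schools will be informed about their group affiliation via e-mail and telephone call immediately after randomization". The pupil check follows: "Before the baseline measurement, pupils will be checked for eligibility and the booklets" are dealt with at the same step. Data assessment confirms: "The baseline assessment (T0) will take place after randomization". Mental health treatment status is listed among the T0 questions (Assessment measures). The protocol states that neither schools nor researchers can be blinded.

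The primary model is for newly detected NSSI at T3. Baseline NSSI enters a secondary analysis as an adjustment variable.

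**The concern.** In an open cluster trial, anything that decides membership of the analysis set should be fixed before the people who ask or answer the question can know the arm. Here the answer that removes a pupil is a self-report collected after the school has been notified. Pupils in psychotherapy plausibly carry a higher NSSI risk than their classmates, so if the two arms identify them with different completeness, the remaining groups differ in risk for reasons unrelated to DUDE.

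The baseline NSSI report has the same timing. If a newly detected case means NSSI at T3 without NSSI at T0, under-reporting at T0 in one arm creates apparent new cases in that arm; the adjusted analysis would carry the same error in its covariate.

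Separately, the two rules give two different data sets. An analyst following the Statistical analysis section keeps the psychotherapy pupils; one following the eligibility section drops them.

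**Working it through.** **1. The plan's own figures.** Inputs from the Sample size section: 2.31% versus 0%, ICC 0.015, 160 analysed pupils per school, 8 schools per group, two-sided 5%, 20% dropout.

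- Recruitment: 160 / 0.8 = 200 per school; 200 × 16 = 3,200. This matches.
- Design effect: 1 + 159 × 0.015 = 3.385. Effective n per group: 1,280 / 3.385 = 378.
- Power: 84.9% with an unpooled z-test, 79.4% with a t reference on 14 df. The stated 80% is within reach, and the power statement is not in dispute here.
- Expected control events: 1,280 × 0.0231 = 29.6, about 30.

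**2. The sequence.** Consent → randomisation → school told its arm → eligibility check and booklet → T0 → DUDE 7 (± 3) days later. Whether psychotherapy is taken from the eligibility check or from the T0 treatment item, it is recorded after notification. So is T0 NSSI.

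**3. The two analysis rules.** The eligibility section calls the psychotherapy pupils participants, and they can have consented before their school was randomised. They are neither dropouts nor missing, since their data are collected, so the imputation rule does not cover them. Nothing in the Statistical analysis section exempts them.

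**4. Effect on power.** The protocol gives no psychotherapy share, so the shares are assumptions. Leaving out 2%, 5% or 10% of the 3,200 (64, 160 or 320 pupils) on top of dropout gives 156.8, 152 or 144 analysed per school. Power goes from 84.9% to 84.6%, 84.3% or 83.7% (z), or from 79.4% to 79.2%, 78.8% or 78.1% (t). Power is not the issue.

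**5. Possible bias from unequal identification, with no true effect.** Assume a share f of pupils in therapy with RR times the risk of the others, and an overall risk of 2.31%. Then

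- r0 = 0.0231 / (1 − f + f × RR) and r1 = RR × r0
- risk after removing a share e of the therapy pupils = [(1 − f) × r0 + f × (1 − e) × r1] / (1 − f × e)

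Worked case, f = 0.08 and RR = 5: r0 = 0.0231 / 1.32 = 0.0175 and r1 = 0.0875. With e = 1 the risk is 1.75%. With e = 0.5 it is (0.0161 + 0.0035) / 0.96 = 2.042%. The difference is 0.292 points.

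| f | RR | one arm identifies all, the other half | one arm identifies all, the other 80% |
|---|---|---|---|
| 3% | 3 | 0.066 | 0.027 |
| 3% | 5 | 0.126 | 0.051 |
| 5% | 3 | 0.108 | 0.044 |
| 5% | 5 | 0.197 | 0.080 |
| 8% | 3 | 0.166 | 0.068 |
| 8% | 5 | 0.292 | 0.120 |

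Values are percentage points. Against the planned 2.31, the first column is 0.066 / 2.31 = 3% to 0.292 / 2.31 = 13%. The arm that identifies fewer therapy pupils shows the higher risk, so the direction depends on which arm that is. The documents give nothing from which to size the T0 NSSI route.

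**The case against.** The defence has real substance. Consent is taken before randomisation, which largely prevents arm-dependent recruitment, a principal threat in open cluster trials. The protocol says that schools are told their arm; it does not say that pupils, who self-report, know it before T0. Being in psychotherapy is a factual status, less open to expectation than a symptom rating. Schools, not pupils, are randomised, and the all-randomised sentence sits in a paragraph about missing data and withdrawal, so dropping pupils who fail a pre-specified criterion can be read as defining the population to which ITT applies. All of this limits the size of the problem. None of it moves the two reports ahead of notification or states which pupils are in the analysis set.

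A reader might infer more, and the documents do not support it:

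- *That pupils who start therapy later are also removed, including those seen under the Emergency procedure.* That section's "if necessary, a treatment offer will be made" concerns care, not the analysis set. The criterion is current therapy and eligibility is checked before baseline. The protocol is merely silent on therapy first reported at T1 to T3.
- *That DUDE itself changes disclosure at T0.* DUDE starts about a week after T0. Only knowledge of allocation could act there.
- *That T0 NSSI decides who is analysed.* Nothing in the protocol removes pupils with NSSI at T0. It may bear on who counts as a new case, and it is a covariate.
- *That giving the booklet before T0 biases the comparison.* Both arms receive the same booklet at the same step, and it is a minimal intervention beside five 90-minute units. It does conflict with Setting and recruitment, which places T0 before the start of treatment.
- *That the bias could reach a fifth of the target.* Losing 6 cases from one arm gives 6 / 1,280 = 0.47 points, 20% of 2.31. But at 3–5 times 2.31% (6.9–11.6%) that means excluding about 52 to 87 pupils, 4–7% of one arm, with no matching exclusion in the other.

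**Conclusion.** The point holds in a limited form. Psychotherapy status and baseline NSSI are both recorded after schools have been told their arm in an unblinded trial, which leaves an avoidable route for post-allocation selection and differential baseline reporting. The eligibility section and the Statistical analysis section also give incompatible rules for the psychotherapy pupils and must be reconciled.

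The size is not known. Under assumed therapy shares of 3–8%, 3–5 times the NSSI risk, and one arm identifying only half of its therapy pupils, the spurious difference is about 0.07 to 0.29 points against the planned 2.31; milder imbalance gives less. There is no evidence that such imbalance will occur, and the loss of power is negligible. The change is worth making because it is cheap and closes the route, not because the trial is invalid without it.

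**What to change.** 1. Record current psychotherapy with the consent form, which is already collected before randomisation, and apply the exclusion once, on that answer.
2. Complete T0 before allocation is released to schools, and hand out the booklet after T0, so that baseline precedes all intervention as Setting and recruitment says.
3. In Statistical analysis, replace the all-randomised sentence with a definition: all consented pupils in randomised schools who were eligible on the pre-allocation answer, with no exclusion for therapy begun later. Align the eligibility section with it.
4. Report the number excluded for psychotherapy by arm, and add one sensitivity analysis that includes these pupils. Their data are collected anyway.

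If the order of steps cannot change, items 3 and 4 are the minimum, with the definition tied to a single stated time point.

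Cost: one added question on the consent form and some text. The practical burden is scheduling T0 before notification in 16 schools over two rounds. The 7 (± 3)-day interval from T0 to the start of DUDE may have to lengthen so that schools can be informed and teachers prepared.

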### Data safety

Participant confidentiality will be ensured by generating unique study identifiers unrelated to participants’ real names. The collected data and the study identifiers will be kept at the data-holding facility and can only be decoded by the principal investigator through a list in which the names and study identifiers are provided together. This list will be stored in a locked cupboard. Decoding can only take place if suicidality occurs in a respective participant (see the “Emergency procedure” section) or the participant would like to be informed about the results of the assessments.

The Institute of Clinical Epidemiology and Biometry, University of Wuerzburg, will operate independently from the study site to control and supervise the data collection and safety. Data will be collected using the EDC system REDCap. This is a secure web application for building and managing online surveys and databases, which is specifically geared to support online and offline data capture for research studies. Data storage and transfer will only be possible on the secured servers of the University of Wuerzburg, and access will be password-protected and strictly limited to authorized personnel only. For data analysis, the anonymized data will be securely transferred to servers of the Chair of Clinical Epidemiology and Biometry, hosted by the University Hospital of Wuerzburg. Computerized assessments guarantee the highest level of data integrity and quality, i.e., missing data will be minimized. However, as with paper-and-pencil questionnaires, human error can occur during data entry. Access to the data via REDCap allows the continuous monitoring of data collection including immediate response in the case of emergency, i.e., suicidality, as well as restoration of all previous states. A Distributed Replicated Block Device (DRBD) will provide synchronous replication of all data during data entry on two separate servers. In addition, full and incremental backups will be conducted following a predefined back-up plan.

### Harms

In view of the non-invasive universal prevention, the risk for the participants is considered marginal. Comparable studies (i.e., SEYLE study or SOSI) showed no iatrogenic effects such as an increase in suicidality or NSSI. Irrespective of the randomization, participating pupils will benefit from a universal prevention that protects against the development of psychopathology and especially NSSI and suicidality. However, an increase in NSSI and suicidality cannot be completely ruled out. Hence, an emergency procedure has been installed in order to help conspicuous pupils (see the “Emergency procedure” section). Nevertheless, there is no obvious risk for participants. The independent Institute of Clinical Epidemiology and Biometry, University of Wuerzburg, will provide expert advice regarding all aspects of data quality. This means that the data could be checked immediately after data entry for adolescents who are potentially at risk, ensuring that the Department of Child and Adolescent Psychiatry, University Hospital of Wuerzburg, can provide them with the necessary help as quickly as possible. Beyond this, the ethics committee and the Ministry of Education and Cultural Affairs will be informed about adverse events, such as suicidal acts, and the further course of the study will then be coordinated with these entities.

The principal investigators will inform surrounding psychiatric hospitals about the study in advance. Information about where to find help as well as necessary contacts will be publicly available on the study homepage and on the information letters given to the pupils beforehand, ensuring that all participants know how to access emergency contacts. Additionally, we will provide consulting addresses and the study staff will also be available by telephone and mail. If any adolescent feels overwhelmed during the data collection or the training, another emergency protocol is in place to offer help right away. In addition, we will be in close contact with the respective educational psychologists throughout the duration of the study to ensure that psychiatric/psychotherapeutic help can be easily provided if needed.

### Ethical issues and dissemination

The study will be conducted in accordance with the Declaration of Helsinki and the rules for physicians of the Bavarian State Medical Association (“Bayrische Landesärztekammer”) in their currently valid version. Participation in the study is voluntary, and all adolescents and their guardians will need to sign an informed consent form. Consent can be withdrawn at any time without stating a reason and without any individual disadvantage for subsequent school matters or medical care. In the case of study withdrawal, previously collected data will be deleted if desired unless data have already been included in the analyses or identification of the individual participant data is no longer possible. The participant list from which pupils can be identified will only be available to the school principal and will be destroyed after T3. In this way, we can assure that data can be fully anonymized. The study protocol has been approved by the ethics committee in Wuerzburg (127/19-me) and the Ministry of Education and Cultural Affairs (IV.7-BO5106/200/12).

In the case of relevant protocol modifications, the ethics committee and the Ministry of Education and Cultural Affairs will be informed immediately and an amendment will be submitted. Access to the protocol and information for the public is ensured through the registration and regular update of the trial in the German Clinical Trials Register (DRKS) (DUDE - the prevention program for schools to reduce self-injurious behavior by enhancing stress tolerance and emotion regulation; DRKS00018945; registration date 01 April 2020).

All confidential information will be subject to the rules of medical confidentiality and in line with the requirements of the European, Federal and State Data Protection Act (Europäische Datenschutzverordnung (EU-DSGVO), Bundesdatenschutzgesetz (BDSG), Landesdatenschutzgesetz (LDSG)). The data will be stored and processed in a pseudonymized manner. No third parties will gain insights into the original data. As reported above, participants can only be identified in the case of emergency or they would like to be informed about the results of the assessments.

The trial results will be disseminated through journal publications and scientific meetings, as well as a broader dissemination if there is evidence of the efficacy of DUDE. The study protocol will be made available to all participating schools. As it concerns data from underage pupils, we are not allowed to make the data set accessible to third parties according to the ethics committee and Ministry of Education and Cultural Affairs. The analysis code is provided as supplemental material each time the results are published. This broad dissemination will occur in cooperation with the KKH and further evaluations of effectiveness beyond a randomized control trial and comparable to stage III or stage IV studies in GCP. The use of professional writers is not intended.

